**Control group**

All patients in the control group will receive symptomatic treatment with antipyretics, adequate hydration, anticoagulation with low molecular weight heparin, intravenous Remdesivir, corticosteroids (intravenous dexamethasone for 5 days or more duration whenever indicated, if oxygen requirement increasing or inflammatory markers are raised), and oxygen support. Patients will receive treatment for comorbid conditions as per guidelines.

**Follow-up**

All study participants will be prospectively followed up during the hospital stay or 10 days whichever is later. Patients will be evaluated telephonically post-discharge till ten days.

**Withdrawal from the study**

Complete and accurate follow-up is extremely important for the duration of the study. The participant, however, may decline to continue protocol-related assessments at any time however every attempt will be made to continue contact by telephone. This does not constitute withdrawal from the study. The reason for withdrawal will be documented for all participants withdrawn from the study. If the vital status is known before hospital discharge, the participant will not be considered lost to follow up.

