**Sample size**

A total sample size of 396 was calculated assuming alpha error=0.05, power 80%, death in the control group of 20% (5), the death rate in the treatment group =15%, a superiority margin of 5%, and a nonresponse rate (loss to follow up) of 10% using sample size calculator <http://riskcalc.org/samplesize/>.

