**Primary outcomes**

The primary outcome will be in-hospital mortality.

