**Statistical Analysis:**

Descriptive statistics will be used to summarize variables. All primary and additional endpoints will be analysed both on intention-to –treat (ITT) basis and on a per-protocol (PP) basis for the study. The ITT population set consists of all patients who have provided informed consent and have been randomized to a treatment group. All patients will be analysed according to the assigned treatment group, regardless of the treatment received.

The PP population set will consist of all patients who have provided informed consent and have been randomized to a treatment group, and who have received only the assigned study treatment, without any major protocol deviation. Participants who do not receive a study treatment, or who receive any treatment other than the study treatment to which they were randomized, will be excluded from the PP population. All participants will be analysed according to the treatment that they received. A supportive analysis of the primary endpoint and all secondary clinical endpoints will also be conducted in the PP population. Wilcoxon rank-sum test will be used for nonnormal distribution. Time-to-event will be compared using the Kaplan-Meier curve and log-rank test. The Cox proportional hazards model will be used to calculate the hazards ratio and 95% Confidence Interval. Safety outcomes will be compared between the groups using Chi-square or Fisher’s exact test.

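### The loss-to-follow-up rule names no time point, does not match the planned follow-up period, and leaves patients transferred alive or leaving against advice unidentifiable.

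*Protocol*

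**What the plan says.** All references are to the protocol.

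- **Withdrawal from the study.** The rule is: "If the vital status is known before hospital discharge, the participant will not be considered lost to follow up". A participant "may decline to continue protocol-related assessments at any time however every attempt will be made to continue contact by telephone", and the section adds: "This does not constitute withdrawal from the study".
- **Follow-up.** "All study participants will be prospectively followed up during the hospital stay or 10 days whichever is later". After discharge: "Patients will be evaluated telephonically post-discharge till ten days".
- **Primary outcomes.** "The primary outcome will be in-hospital mortality". No day is fixed.
- **Sample size.** The total of 396 includes "a nonresponse rate (loss to follow up) of 10" per cent.
- **Statistical Analysis.** "The ITT population set consists of all patients who have provided informed consent and have been randomized to a treatment group". Kaplan-Meier, log-rank and Cox methods are named for time-to-event data. The protocol gives no censoring rule.
- **Blinding.** Participants, staff, data collectors and outcome evaluators all know the assigned group.
- **Appendix-I, Proforma.** It holds admission and discharge dates, a mobile number, and yes/no items for in-hospital death, the clinical secondary events and the safety events. It has no field for how the patient left, for vital status at day 10, or for the date of the last assessment.

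No section mentions transfer to another hospital or departure against advice.

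**The concern.** A loss-to-follow-up rule should say by when an outcome must be known. This one asks only that vital status be known at some moment before discharge, and that is true of any admitted patient. The label therefore separates almost no one from anyone else, and it is not tied to the follow-up period that the protocol sets elsewhere.

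The weak place is a departure that is neither a medical discharge nor a death. Someone moved or taken home alive while still ill has not died in this hospital and is not lost under the rule. If that patient dies days later, neither the rule nor the form brings the death to light. Because everyone knows the allocation, the number and type of such departures can differ by arm, and a difference in departures could then appear as a difference in mortality, or mask one. A statistical analysis plan could set scoring and censoring rules, but it could not apply them to information the form never collected.

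**Working it through.** **1. The rule against the follow-up period.** Day 10 is taken as counted from entry; the Follow-up section does not name the origin.

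| Patient | Lost under the rule? | Planned follow-up completed? | In-hospital mortality |
|---|---|---|---|
| Medically discharged day 5, reached at day 10 | No | Yes | Known: no death |
| Medically discharged day 5, never reached | No | No | Known: no death |
| Transferred or left against advice day 5, never reached | No | No | Recorded as no in-hospital death; the course after leaving is unknown |
| Declines assessments, stays in hospital | No | Vital status yes, assessments no | Known |

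Rows 2 and 3 show the mismatch with the Follow-up section. Only row 3 touches the primary outcome. Row 4 concerns secondary, laboratory and safety data only. On the proforma, row 3 cannot be told apart from rows 1 and 2.

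**2. The 10% allowance.** The planned total can be reproduced with a one-sided 5% margin formula that adds the 5-point margin to the 5-point difference:

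- (0.20×0.80 + 0.15×0.85) × (1.645 + 0.842)² / 0.10² = 0.2875 × 6.18 / 0.01, which rounds up to 178 per arm, or 356 in total
- 356 / 0.90 = 395.6, so 396

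The allowance is thus a real part of the total (396 − 356 = 40 patients). Whether that formula suits a superiority trial is a separate matter.

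**3. Illustration of size.** The inputs from the protocol are 396 patients and mortality of 20% and 15%. Assumed, because the documents give nothing: 1:1 allocation (198 per arm), the share leaving alive early, the later mortality of those who leave (40%, range 30% to 50%), and that all of them are scored as survivors.

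Recorded rate = true rate − (share leaving × later mortality).

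- *Balanced, 5% in each arm.* Deaths not seen: 198 × 0.05 × 0.40 = 3.96 per arm, against 198 × 0.20 = 39.6 and 198 × 0.15 = 29.7 expected. Recorded rates are 18.0% and 13.0%, so the difference stays at 5.0 points.
- *No true effect (20% in both arms), 2% of control and 8% of intervention leaving.* Control 20 − 2×0.40 = 19.2%; intervention 20 − 8×0.40 = 16.8%. The spurious difference is 2.4 points. At 30% later mortality it is 19.4 − 17.6 = 1.8; at 50% it is 19.0 − 16.0 = 3.0.
- *Error rate in that case.* SE = √[(0.192×0.808 + 0.168×0.832)/198] = 0.0386, and 0.024/0.0386 = 0.62. A two-sided 5% test rejects with probability P(Z > 1.34) + P(Z < −2.58) ≈ 9.5%. The range is 7.5% to 12.3% for 30% to 50% later mortality.
- *Reversed pattern with a true effect, 8% of control and 2% of intervention leaving.* 20 − 8×0.40 = 16.8% and 15 − 2×0.40 = 14.2%, so 5 points shrink to 2.6.
- *Other assumptions, no true effect, 10% of one arm and 5% of the other leaving, 50% later mortality.* 15.0% against 17.5%, or 2.5 points.

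**The case against.** The strongest reply is that the rule fits the outcome. If the sentence means vital status known up to discharge, it fully determines in-hospital mortality, and a patient discharged well on day 5 is correctly a non-event whether or not anyone answers the telephone. The safety endpoints are also confined to the hospital stay, and no named endpoint depends on the day-10 call. This stands for routine discharge. It does not settle transfer or departure against advice, where being alive on leaving says little about the course that in-hospital mortality is meant to capture.

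A reader might infer more than the documents support:

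- *That the protocol scores early leavers and decliners as event-free on every outcome.* No sentence says so. The rule decides only who is called lost. Time-to-event methods are planned, and censoring may be set in a statistical analysis plan that is not shown. Censoring at departure would still assume that leaving is unrelated to prognosis.
- *That items for decliners default to no.* The form's fields are blank yes/no boxes. A decliner who stays in hospital is still under care, and telephone contact continues.
- *That the 10% loss in the sample size contradicts the rule.* It is a planning allowance, not a definition, and the withdrawal section itself foresees withdrawn participants. At most, the rule would leave little loss to report against it.
- *That a bias of known size has been shown.* The departure rates and the fourfold imbalance are assumptions.

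**Conclusion.** The point holds in a limited form. The rule has no time anchor and is out of step with the protocol's own follow-up period. For medically discharged patients this does no harm to the primary outcome. For patients transferred alive or leaving against advice it leaves a real gap: the rule treats them as complete, in-hospital mortality counts them as survivors, and the proforma can neither identify them nor record what followed. Open-label care makes an imbalance between arms possible; nothing in the documents shows that one will occur.

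The size cannot be derived from the protocol. With 2% against 8% leaving and 40% later mortality, all scored as survivors, it would be about 2.4 points, roughly half the 5-point effect assumed in the sample size. With balanced departures and equal later mortality the absolute difference would not move. The change is worth making because it is cheap and because the missing information cannot be recovered afterwards.

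**What to change.** 1. Reword the sentence in the withdrawal section as two definitions. Follow-up for in-hospital mortality is complete if vital status is known at discharge, meaning medical discharge or death. Follow-up for the planned period is complete if vital status is known at the later of discharge and day 10. A patient medically discharged but not reached at day 10 is then incomplete for the period, not for the primary outcome.
2. Add three fields to the proforma: mode of leaving (medical discharge, transfer, against advice, death), vital status at day 10, and date of last assessment.
3. Keep in-hospital mortality as the primary outcome. Add an ITT sensitivity analysis of death from any cause to the later of discharge and day 10. Apply it to all patients in both arms, so that deaths after departure are not counted for some types of leaver only.
4. Report transfers, departures against advice and unknown day-10 status by arm.
5. For patients who decline assessments, treat secondary and safety items not observed after the last assessment as missing.

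The cost is one reworded rule, three fields and one added analysis. The telephone contact is already planned, and treatment and sample size do not change. The downsides are that reported loss to follow-up will be above zero, and that deaths after day 10 in patients who left early will remain unseen.

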**Statistical Analysis:**

Descriptive statistics will be used to summarize variables. All primary and additional endpoints will be analysed both on intention-to –treat (ITT) basis and on a per-protocol (PP) basis for the study. The ITT population set consists of all patients who have provided informed consent and have been randomized to a treatment group. All patients will be analysed according to the assigned treatment group, regardless of the treatment received.

The PP population set will consist of all patients who have provided informed consent and have been randomized to a treatment group, and who have received only the assigned study treatment, without any major protocol deviation. Participants who do not receive a study treatment, or who receive any treatment other than the study treatment to which they were randomized, will be excluded from the PP population. All participants will be analysed according to the treatment that they received. A supportive analysis of the primary endpoint and all secondary clinical endpoints will also be conducted in the PP population. Wilcoxon rank-sum test will be used for nonnormal distribution. Time-to-event will be compared using the Kaplan-Meier curve and log-rank test. The Cox proportional hazards model will be used to calculate the hazards ratio and 95% Confidence Interval. Safety outcomes will be compared between the groups using Chi-square or Fisher’s exact test.

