**Introduction**

COVID-19 has presented a major threat to public health worldwide. The case fatality rate of COVID-19 is 2%–3%, but the pandemic associated with COVID-19 has been far more severe. SARS-CoV-2 is highly contagious and most individuals within the population are susceptible to infection(1).

SARS-CoV-2 is a single-stranded RNA virus (2). The viral infection is cytopathic to human cells, by binding to membrane-bound angiotensin-converting enzyme 2 (ACE2). ACE2 is expressed abundantly on vascular endothelial cells. The endothelial dysfunction is associated with vasoconstriction, inflammation, permeability, and coagulation(3). The immune-mediated injury may play a critical role in the pathogenesis of COVID-19. In severe forms of COVID-19, the inflammatory cascade may lead to a cytokine storm. The cytokine storm is believed to be a key factor driving both ARDS and extra-pulmonary organ failure (1)

COVID-19 represents a spectrum of clinical manifestations that typically include fever, dry cough, myalgia, weakness, and fatigue, often with pulmonary involvement (1). The majority (81%) of patients had mild manifestations, 14% had severe manifestations, and 5% had critical manifestations. Older adults and those with comorbidities are believed to be at an elevated risk of complications (2). The complications of COVID-19 include pneumonia (75%), acute respiratory distress syndrome (15%), acute liver injury, acute cardiac injury, prothrombotic coagulopathy, acute kidney injury, neurologic manifestations, including impaired consciousness and acute cerebrovascular disease, and shock (4). The disease is associated with lymphopenia, elevated inflammatory markers, and abnormal coagulation parameters(3).

Different treatment modalities might likely have different efficacies at different stages of illness and in different manifestations of the disease. Viral inhibition would be expected to be most effective early in infection, while, in hospitalized patients, immunomodulatory agents may be useful to prevent disease progression and anticoagulants may be useful to prevent thromboembolic complications. Various drugs like antivirals, antibodies, anti-inflammatory agents, targeted immunomodulatory therapies, anticoagulants, and antifibrotics are being evaluated for the management of COVID-19 with limited success so far(4).

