**Outcome and measurement**

Data collection is done by the specially trained nursing officers of the hospital. Patients’ demographic data and clinical data including age, sex, comorbidities, baseline vital information, saturation, treatment received, type of oxygen support, baseline and follow-up investigation information, outcome, and safety endpoint information will be recorded on structured proforma.

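### The only listed test that fits in-hospital death is an unadjusted log-rank test; it is valid, but it forgoes modest precision available from age, comorbidity and admission SpO2, which are already recorded

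*Protocol*

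**What the plan says.** The Statistical Analysis section of the protocol states: "Time-to-event will be compared using the Kaplan-Meier curve and log-rank test". It continues: "The Cox proportional hazards model will be used to calculate the hazards ratio and 95% Confidence Interval". It does not name the event, mentions no strata, and says nothing for or against covariates in the Cox model. The other methods listed are the Wilcoxon rank-sum test for non-normal data and chi-square or Fisher's exact test for safety outcomes.

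Other sections bear on this:

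- Primary outcomes: "The primary outcome will be in-hospital mortality".
- Introduction: "Older adults and those with comorbidities are believed to be at an elevated risk of complications".
- Outcome and measurement: the data collected are described as "including age, sex, comorbidities, baseline vital information, saturation", among other items.
- Appendix-I proforma: age on the opening form, 13 comorbidities in section 2, respiratory rate in section 4, and admission SpO2 in section 5. SpO2 has two fields, one without oxygen support and one on a face mask.
- Randomization: blocks of four, with no stratification factor named.
- Sample size: "A total sample size of 396 was calculated assuming alpha error=0.05, power 80"%, with "death in the control group of 20"% and "the death rate in the treatment group =15"%.

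**The concern.** The protocol identifies risk factors for a worse course and records them at admission, but neither the allocation scheme nor the named test uses them. Differences in baseline risk between patients then stay in the error variance of the comparison that answers the first objective. The trial expects only about 70 deaths, so precision that can be had from data already collected is worth taking.

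Timing matters too. Under Blinding, the staff who collect data and evaluate outcomes know the group. If the arms turned out to differ visibly in age or saturation, an adjusted analysis chosen at that stage would be open to the charge of selection. One fixed beforehand would not.

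**Working it through.** **1. Which method applies to the primary outcome.** Chi-square or Fisher's test is assigned to safety outcomes and Wilcoxon to non-normal measurements. That leaves log-rank and Cox for in-hospital death. This is a reading by elimination, because the section does not tie them to mortality by name.

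**2. The plan's own figure.** The stated 396 reproduces with one-sided alpha 0.05 and a distance of 5 + 5 = 10 points (effect plus margin):

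- n per arm = (1.645 + 0.842)² × (0.20×0.80 + 0.15×0.85) / 0.10² = 178 (rounded up)
- total 356; 356/0.9 = 396 (rounded up)

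Covariates are not an input, so this point neither contradicts nor changes the 396.

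**3. Baseline precision and power, 198 per arm (1:1 assumed, as the ratio is not stated), 20% vs 15%.**

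- Expected deaths: 198×0.20 + 198×0.15 = 69.3
- SE of the risk difference: sqrt((0.16 + 0.1275)/198) = 0.038, or 3.8 points
- Power, two-sided 0.05: 25.7% (two proportions). For log-rank, HR = ln 0.85/ln 0.80 = 0.728 and power is 26.1%

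**4. Gain from adjustment.** The protocol gives no prognostic strength, so a range is assumed. The outcome was simulated from a logistic model with one standard-normal risk score, 4,000 trials per row. The unadjusted two-proportion test was compared with the adjusted logistic test, and variance was taken for the standardised risk difference.

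| Score coefficient | AUC | Variance cut | Power unadjusted | Power adjusted |
|---|---|---|---|---|
| 0.6 | 0.66 | 5.2% | 27.2% | 27.4% |
| 0.8 | 0.71 | 8.7% | 25.9% | 27.6% |
| 1.0 | 0.75 | 12.3% | 25.5% | 28.5% |
| 1.3 | 0.79 | 17.8% | 26.5% | 31.0% |

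Type I error of the adjusted test was 4.5 to 5.0%. In patients, 1/(1 − 0.052) = 1.055 and 1/(1 − 0.178) = 1.217, so the gain is worth about 22 to 86 patients on 396.

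A separate simulation (logistic Wald tests, 4,000 trials each) gave, unadjusted vs adjusted:

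- 24.7% vs 25.4% at coefficient 0.5
- 24.8% vs 28.2% at 1.0
- 25.4% vs 31.6% at 1.5

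The top of the range, about 6 points, comes from coefficient 1.5, which is stronger than any row of the table.

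As an analytic cross-check, information was inflated by 1/(1 − R²). Power is 26.8% at R² = 5% and 31.0% at 20% for proportions, and 27.2% and 31.4% for log-rank. An R² of 30%, beyond the 18% variance cut at AUC 0.79, would give 34.6% for proportions.

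**5. Validity of the unadjusted test.** In 20,000 null trials per scenario, with covariate coefficients from 0 to 1.5, its type I error was 4.9 to 5.1%.

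**6. Size of a chance imbalance.** Assume an age SD of 15 years. The SE of the difference in mean age is 15×sqrt(2/198) = 1.51 years, so P(|difference| ≥ 2) = 2(1 − Φ(2/1.51)) = 0.185. At an assumed odds ratio of 1.6 to 2.0 per decade, a 2-year gap shifts mortality by ln(1.6 to 2.0) × 0.2 × 0.175 × 0.825 = 1.4 to 2.0 points. Against the SE of 3.8 points that is 0.4 to 0.5 SE.

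**The case against.** The strongest reply is that nothing here is wrong. An unadjusted comparison in a randomised trial is valid, simple randomisation in blocks is an accepted design, and covariate lists are commonly left to a statistical analysis plan, which is not shown. Much of that stands, and it rules out four stronger readings.

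- *The protocol fixes a Cox model without covariates.* It does not. It is silent, and silence about a covariate list is no finding. The point rests on the named log-rank test, which uses no baseline information unless stratified.
- *The mortality test is expressly fixed as log-rank.* Mortality is not named beside it. That is inferred by elimination (step 1).
- *Chance imbalance could create or hide the effect uncorrected.* The shift in step 6 is about half a standard error, in either direction, and needs an imbalance with 18% probability. The type I error and the confidence interval already allow for it.
- *Adjustment would rescue the power.* A test with about 26% power stays underpowered after a gain of a few points.

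The size is also uncertain. AUC, age SD and odds ratio per decade are assumptions. Eligibility (SpO2 below 94% on room air; ARDS, shock, sepsis and acute renal failure at presentation excluded) narrows the spread of risk, so the upper AUC values may not be reached. The Introduction speaks of complications, not specifically death. The simulations use one correctly specified score and binary-outcome models; for log-rank there is only the analytic approximation. Finally, admission SpO2 has two proforma fields, and values on and off oxygen are not interchangeable.

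What the reply does not remove is that a test has been named, it ignores recorded prognostic information, and a better-performing alternative is available at little cost.

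**Conclusion.** The point holds as an inexpensive improvement to a stated choice of method, not as an error of validity. The only listed method that fits the primary outcome leaves unused the factors that the protocol itself flags and collects. Under an assumed AUC of about 0.66 to 0.79, adjustment reduces the variance of the risk difference by roughly 5 to 18%. The power gain over that range is about 0 to 5 points, and about 6 at the strongest coefficient tried, from a base of about 26%. At the low end the benefit is negligible.

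It leaves the sample-size problem untouched. By the usual two-sided formula, 20% vs 15% at 80% power needs 906 per arm, or 1,812 in total, and 1,812/0.9 = 2,014 with the planned loss, against 396.

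**What to change.** In Statistical Analysis, name the primary comparison of in-hospital death as adjusted for three admission variables:

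- age, as a continuous variable;
- comorbidity count, from proforma section 2;
- admission SpO2 without oxygen support, from proforma section 5.

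Report the adjusted effect together with a standardised risk difference and its 95% CI. Keep the log-rank or unadjusted result as a sensitivity analysis. Fix the covariates and their coding before outcome data are tabulated by arm. If a statistical analysis plan already contains such a list, align the protocol with it.

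With about 69 deaths and four coefficients (arm plus three covariates), there are about 69/4 = 17 deaths per coefficient, so the model is small enough.

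The cost is a short addition to the text; no new data, patients or procedures are needed. There are two small burdens. The adjusted odds or hazard ratio is conditional on the covariates, so the standardised risk difference must be reported beside it. Room-air SpO2 may be missing for patients who arrive on oxygen, so a simple handling rule, applied without regard to arm, has to be written down as well.

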**Method and Materials**

**Objectives**

To test whether triple therapy with aspirin, atorvastatin, and nicorandil is superior to usual care in SARS-CoV-2 infected patients in improving outcome.

To find out the safety of triple therapy in SARS-CoV-2 infected patients.

**Study Design**: Single-centre, prospective, two-arm parallel design, open-label randomized control superiority trial.

**Place of Study**: The study will be conducted at the covid centre of [name] Government Medical College Tanda Kangra, Himachal Pradesh India, converted into a dedicated COVID-19 management centre since August 2020.

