**Safety endpoints**

Hepatotoxicity (ALT/AST > 3x ULN; hyperbilirubinemia), myalgia—muscle ache or weakness without creatine kinase (CPK) elevation, myositis—muscle symptoms with increased CPK levels (3-10)ULN, rhabdomyolysis—muscle symptoms with marked CPK elevation (typically substantially greater than 10 times the upper limit of normal [ULN]) and with creatinine elevation (usually with brown urine and urinary myoglobin), minor Bleeding (BARC bleeding type 1 and 2 or major Bleeding (BARC bleeding type 3 –5 ) will be safety endpoints observed during the hospital stay.

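### The only inferential method fixed for the safety objective is a test of no difference, which cannot show how much harm remains compatible with the data; risk differences with 95% intervals would show it

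*Protocol*

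**What the plan says.** The Objectives section lists two aims. The first is superiority of the triple therapy over usual care; the second reads "To find out the safety of triple therapy in SARS-CoV-2 infected patients". No hypothesis, margin or success rule is attached to the second aim.

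The Safety endpoints section lists hepatotoxicity, three grades of muscle toxicity, minor bleeding and "major Bleeding (BARC bleeding type 3 –5"). It adds that these "will be safety endpoints observed during the hospital stay". No expected rates are given.

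The Statistical Analysis section opens with "Descriptive statistics will be used to summarize variables", which is not limited to efficacy variables. For safety it then says "Safety outcomes will be compared between the groups using Chi-square or Fisher’s exact test". Its one confidence interval belongs to a different analysis: "The Cox proportional hazards model will be used to calculate the hazards ratio and 95% Confidence Interval".

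The Sample size section derives 396 from death rates of 20% and 15%, a 5% margin, alpha 0.05, 80% power and 10% loss. Safety plays no part in it.

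**The concern.** A chi-square or Fisher test asks whether the data conflict with equal risk in the two arms. A small p-value indicates a difference. A large one means only that the data did not settle the matter, and it does not separate a truly small excess from a trial too small to see a large one. An objective of finding out how safe a treatment is calls for an estimate of the excess and its uncertainty.

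Bleeding is where this matters most. Under Intervention groups, both arms receive low molecular weight heparin and the intervention arm adds aspirin, so an increase in bleeding is a plausible harm. If major bleeding is uncommon, the planned tests will usually be non-significant even when the risk has doubled. A report that follows the protocol literally could give counts and p-values and leave readers to treat non-significance as reassurance.

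**Working it through.** **Inputs.** Total 396 and loss 10% come from Sample size. The allocation ratio is not stated; 1:1 is assumed, which is compatible with the block size of four under Randomization. That gives 396/2 = 198 per arm, or 198 × 0.9 ≈ 178 after loss. The protocol states alpha 0.05 without sidedness; two-sided 0.05 is assumed for the safety tests. The control rate of major bleeding is not given, so 1% to 5% is assumed, with a doubling in the intervention arm.

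**The plan's own figure.** 396 can be reproduced, as a mortality calculation only. With one-sided alpha 0.05 and the 5-point margin added to the 5-point difference:

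n = (1.645 + 0.842)² × (0.20×0.80 + 0.15×0.85) / 0.10² = 177.7, so 178 per arm; 2 × 178 / 0.9 = 395.6, so 396.

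Whether that is a sound basis for the mortality comparison is a separate matter. Here it confirms that no safety rate entered the sample size.

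**Power of the planned tests.** For n per arm, control risk p0 and intervention risk p1, power is the sum, over all event counts x and y, of Bin(x; n, p0) × Bin(y; n, p1) for those pairs where the test gives p ≤ 0.05. The miss rate is 1 minus power. Chi-square is without continuity correction.

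| Control vs intervention | Chi-square, 198 | Fisher, 198 | Chi-square, 178 | Fisher, 178 | Missed |
|---|---|---|---|---|---|
| 1% vs 2% | 0.115 | 0.044 | 0.107 | 0.034 | 89–97% |
| 2% vs 4% | 0.208 | 0.129 | 0.186 | 0.112 | 79–89% |
| 3% vs 6% | 0.299 | 0.222 | 0.273 | 0.193 | 70–81% |
| 5% vs 10% | 0.479 | 0.401 | 0.436 | 0.357 | 52–64% |

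The last column runs from chi-square at 198 to Fisher at 178.

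**What an interval adds.** Suppose 4 of 198 control and 8 of 198 intervention patients have a major bleed (2.02% and 4.04%). The pooled risk is 12/396; chi-square is 1.375, p = 0.24, and Fisher gives p = 0.38. For the Newcombe interval, the Wilson limits are 0.79% to 5.08% (control) and 2.06% to 7.77% (intervention). The difference is 2.02 points, with:

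- lower limit: 2.02 − √[(4.04 − 2.06)² + (5.08 − 2.02)²] = −1.6 points
- upper limit: 2.02 + √[(7.77 − 4.04)² + (2.02 − 0.79)²] = +5.9 points

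The p-value says not significant. The interval says that anything from a small reduction to an excess of nearly 6 per 100 fits the data.

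Even with equal counts, 4 vs 4, the risk ratio interval is exp(±1.96 × √(2/4 − 2/198)) = 0.25 to 3.9, so a doubling is not excluded.

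**The case against.** The case against is substantial.

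- **The test is standard, and a SAP may add intervals.** Chi-square or Fisher is a usual comparison for binary safety outcomes, and nothing in the protocol forbids an interval. Only the protocol is at hand, and interval details are often left to a SAP. This stands against calling the sentence an error. It does not remove the point, because the protocol itself fixes the method for a named objective, and that method does not give the size of the excess.
- **Descriptive summaries are planned too.** This stands: safety is not judged by tests alone, and a reader with counts per arm could work out the interval. The protocol still does not commit the trial to reporting it or to basing the conclusion on it.
- **Low power for uncommon harms is ordinary** in a trial sized on mortality, and a formal safety margin is not usual for a descriptive objective. Both stand. The remedy needs neither more patients nor a margin.

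Three stronger readings are tempting but unsupported. A reader might infer that the protocol treats a non-significant p-value as proof of safety; no text says so, and the objective claims no demonstration of safety. A reader might take a miss rate of 8 to 9 in 10 for a doubling as a property of the trial; it depends on the assumed control rate and falls to 52–64% at 5%. Nor would a tripling very probably be missed: 2% vs 6% is missed 46–62% of the time by the same calculation, close to even odds.

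**Conclusion.** The point holds as a limited one. For its second objective the protocol names a test of no difference as the only inferential method. At this sample size the test would miss a doubling of major bleeding more often than not across assumed control rates of 1% to 5%. The figures rest on 1:1 allocation, two-sided 0.05, 178 to 198 patients analysed per arm, and control rates that are assumptions because the protocol gives none.

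The consequence is a risk of misplaced reassurance, not a rule written into the plan. The upper limit of 5.9 points in the example might tempt a reader to set it against the assumed 5-point mortality benefit. The documents give no basis for weighing one major bleed against one death, so that benefit should not serve as a threshold for bleeding. Severity is minor: a cheap improvement.

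**What to change.** In Statistical Analysis, state that for each safety endpoint the trial will report:

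- the number of patients with an event in each arm;
- the risk difference, intervention minus control, with a two-sided 95% confidence interval (for example Newcombe).

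State also that the safety conclusion will rest on that interval, that chi-square or Fisher p-values are descriptive, and that p > 0.05 is not evidence of safety. No margin or benefit-based threshold is needed.

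The cost is two or three sentences, with no extra patients, data or staff. The small downside is that the trial may have to report that a relevant excess of harm is not excluded.
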